## Methods/Design

### Overview

The study is a multi-center, double-blind, randomized controlled trial comparing two group interventions: the BEST MOOD program and a treatment-as-usual supportive parenting program known as Parenting Adolescents Support Training (PAST). Both interventions are for families of youth who present with a unipolar mood disorder, here defined as major or minor adolescent depression or dysthymia. In both treatment conditions, families receive eight sessions of treatment delivered over two hours per week. The trial will run across several sites in both metropolitan Melbourne and the regional Victorian city of Geelong. Families will be recruited primarily from the intake service of a large government run mental health service in the eastern region of Melbourne (Eastern Health’s Child and Youth Mental Health Service; CYMHS), but community referrals will also be accepted from schools and community based health and mental health services, and via promotion of the study at community forums. At the completion of the interventions, face-to-face interviews will be conducted to better understand the level of engagement of participants with the treatment following intake/assessment. The aims of the qualitative component of the study are to explore the phenomena of not taking-up treatment, discontinuing treatment after commencement, completing treatment and benefiting from treatment, and the perceived influencing factors on these outcomes.

The primary outcome measure will be rates of remission of depressive disorder (major, minor, or dysthymia), according to a structured diagnostic clinical assessment, utilizing modules from the Structured Clinical Interview for *DSM-IV Childhood Diagnoses* KID-SCID; [28]. The secondary outcome measures will include: adolescent mental health (parent and self-reported), parent mental health, the young person’s level of engagement with mental health services, the parent-child relationship, and the therapist-client working alliance. Psychologists, social workers, and postgraduate psychology students who will be trained and supervised in one of the interventions for an equivalent amount of time, will deliver treatment. Therapists and assessors are blinded to the content of the alternate intervention, and are blinded to whether they are delivering the experimental or control condition in the study.

### Aims and hypotheses

The primary aim of the trial is to evaluate the efficacy of the two interventions as: (a) treatments for youth mental health problems and (b) as methods of engaging youth in treatments. The secondary aims will include: (c) to build capacity and increase service integration across several service delivery sectors by providing evidence based intervention programs for youth and their families; (d) to influence national and state government policy on the use of family based approaches in the field of youth mental health; and (e) make use of the study partnerships for national promotion and dissemination of family-based treatment models for youth mental health.

The primary study hypothesis is that youth in the BEST MOOD intervention will demonstrate significantly greater rates of remission of depressive disorders (major, minor, or dysthymia), than youth in the PAST intervention. Secondary hypotheses include: (a) that parental and youth mental health and relationships will improve in response to both interventions, but significantly more so in response to BEST MOOD; (b) that greater treatment engagement for youth will be associated with greater improvements in youth mental health outcomes; and (c) that youth in the BEST MOOD condition will report greater treatment engagement than youth in the PAST condition.

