### Eligibility criteria

#### Inclusion criteria

Families will be included in the study where there is an adolescent aged 12 to 18 years who is currently presenting with a depressive disorder. Specifically, the young person must, at the time of assessment, meet the criteria for either major depressive disorder, minor depressive disorder, or dysthymic disorder as assessed via current *DSM-IV* criteria.

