### Parenting Adolescents Support Training (PAST)

The PAST intervention will act as the treatment-as-usual control condition in this trial. Parents will attend a professionally facilitated parenting group which uses supportive counselling techniques. The PAST intervention runs for eight, weekly two-hour sessions. Youth and siblings (aged 12 and over) are invited to join in the fifth week. This intervention has been manualized for the purpose of this study. The content of PAST has been designed to equate with standard practices in currently available services in Australia, where if any service is offered, it is likely to consist of a parent support group. The development of this intervention was guided by the current protocols for the family mental health support services in Victoria, Australia. The PAST intervention offers: (a) supportive counselling to assist parents to articulate and identify concerns and (b) psycho-education to increase parents’ knowledge about youth mental health problems. The main content of the PAST group is support and the opportunity to share experiences and ideas as well as receiving contact with a mental health professional.

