### Statistical analysis plan

Repeated measures binomial data will be analyzed over three time points using a binary logistic regression within the Generalized Linear Mixed Model (GLMM). The model will be fitted in STATA (xtmelogit). For any continuous-scale data we will use a linear mixed model approach in STATA. For both types of data we will explore variance-covariance structures for the evaluations within an individual. Clinical significance and an index of reliable change will be calculated for each measure using the criteria of Jacobson and Truax [46]. Findings will be analyzed in terms of standardized mean differences and effect sizes achieved will be compared to existing high quality trials to determine relative efficacy of this intervention. Multivariable multilevel models will also explore other covariates on the relationship between treatment arm and study outcomes, with a view to improving the intervention and specifying its ideal target population. Data will be stored in a locked cabinet, and a password protected computer file will contain de-identified (coded) data. A proportion of the data will be double-entered, and range checks will be performed for accuracy checking. Intention-to-treat analysis will be used with the last observation carried forward as a conservative estimate of outcome when data are missing at follow-up.

In addition, analysis of qualitative data from the transcribed interviews of participants who did not take up the option of treatment following intake/assessment, discontinued treatment, or completed treatment will be undertaken. Thematic analysis of participants’ accounts of their experience of the intake/assessment process and reasons for either engaging with or distancing themselves from the treatment offered will be undertaken. Meanings participants assign to the process will also be extracted from the data. Analysis of the data relevant to the phenomena of interest will assist in the identification of barriers to engagement and change for families.

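### Improvement in response to both programs, and the absolute efficacy of either, cannot be tested with two active arms; the between-arm comparison is unaffected

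*Protocol article*

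**What the plan says.** All references are to the protocol article.

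- **Aims and hypotheses, primary aim:** "The primary aim of the trial is to evaluate the efficacy of the two interventions as: (a) treatments for youth mental health problems". Both programs are named.
- **Aims and hypotheses, secondary hypothesis (a):** "that parental and youth mental health and relationships will improve in response to both interventions, but significantly more so in response to BEST MOOD". It has two clauses: both arms improve because of what they receive, and BEST MOOD improves more.
- **Aims and hypotheses, primary hypothesis:** BEST MOOD youth will show "significantly greater rates of remission of depressive disorders (major, minor, or dysthymia), than youth in the PAST intervention". This is purely between-arm.
- **Overview:** the study is a "randomized controlled trial comparing two group interventions". No untreated or wait-list arm is described.
- **Section on PAST:** "The PAST intervention will act as the treatment-as-usual control condition in this trial".
- **Inclusion criteria:** each family has "an adolescent aged 12 to 18 years who is currently presenting with a depressive disorder".
- **Sample size and power:** the secondary hypotheses on continuous outcomes are powered on the interaction of arm and time.
- **Statistical analysis plan section:** a reliable change index is calculated for each measure, and "effect sizes achieved will be compared to existing high quality trials to determine relative efficacy of this intervention".

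**The concern.** The first clause of hypothesis (a) is a causal statement about each arm separately, including the control arm. The only evidence the trial can bring to it is change from baseline within an arm. No youth is in remission at T1, because a current disorder is required for entry, so any later remission counts as improvement whatever caused it. Follow-up runs to 20 weeks. Other care is not ruled out: the exclusion covers only youth already fully engaged in a service that the family finds adequate, and service and medication use are recorded as engagement data.

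This matters most if the arms do not differ. The design then supports only the statement that no difference was shown. The wording of the aim and hypothesis leaves room to report that both programs worked, although the data would fit equally well with neither having any effect. Aims (d) and (e) look ahead to policy influence and national promotion, so such a conclusion could travel.

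**Working it through.** **1. What each statement needs**

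| Statement | Comparison needed | Available here? |
|---|---|---|
| Primary hypothesis (remission greater with BEST MOOD) | BEST MOOD against PAST | Yes, randomized |
| Hypothesis (a), greater improvement with BEST MOOD | Between-arm difference in change | Yes, randomized |
| Hypothesis (a), improvement in response to both | Each arm against no program | No |
| Aim (a), read as efficacy of each program | Each arm against no program | No |
| Aim (a), read as relative efficacy | BEST MOOD against PAST | Yes, randomized |

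The reliable change index judges whether an individual's change exceeds measurement error, not what caused it. Comparison with other trials is not randomized, so it cannot supply the missing reference.

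**2. How often both arms would appear to respond when neither program works**

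Inputs from Sample size and power: n = 57 per arm, two-sided alpha 0.05, within-person correlation r = 0.20, and therapy-group ICC 0.07 (both correlations from the secondary-outcome paragraph). Assumptions of this review, because the protocol gives no figure: natural improvement d of 0.2 to 0.5 SD, the same in both arms, and a therapy group size of 8.

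Test: paired t within each arm, with dz = d / √(2(1 − r)) and noncentrality dz × √57. With r = 0.20, √(2 × 0.80) = 1.265. For d = 0.5, dz = 0.395 and the noncentrality is 2.98. The arms are treated as independent, so the joint probability is the square of the one-arm probability.

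Clustering is approximated by the design effect 1 + (8 − 1) × 0.07 = 1.49, which reduces the noncentrality by a factor of √1.49.

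| Natural change (SD) | One arm, no clustering | Both arms, no clustering | One arm, design effect 1.49 | Both arms, design effect 1.49 |
|---|---|---|---|---|
| 0.2 | 22% | 5% | 16% | 3% |
| 0.3 | 42% | 18% | 30% | 9% |
| 0.4 | 65% | 42% | 49% | 24% |
| 0.5 | 83% | 70% | 67% | 45% |

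A higher within-person correlation raises these figures. At an assumed r = 0.50 without clustering, both arms are significant in 10%, 37%, 71% and 92% of trials.

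**3. The whole of hypothesis (a) under the same conditions**

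Natural recovery acts alike on both randomized arms and cancels in their difference. A two-sided 5% test favors BEST MOOD by chance in 2.5% of trials. Requiring significant improvement in both arms as well can only lower that. In simulation without clustering at r = 0.50, the full hypothesis was met in 0.08% of trials at d = 0.3, 1.4% at d = 0.5 and 2.5% at d = 0.8.

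**The case against.** The strongest objection is that hypothesis (a) is a conjunction. A reader might infer that natural recovery would confirm the hypothesis, making it close to self-confirming. The document does not support that: the second clause requires a between-arm difference, and recovery common to both arms yields one in BEST MOOD's favor only at the 2.5% chance rate. This objection stands, and it limits the point to the first clause.

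Four further objections stand in part.

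- **Aim (a) attributes nothing.** It says efficacy will be evaluated, in a trial described as a comparison with PAST named as the control, so a relative reading is natural. That is accepted. The wording still names both programs and does not exclude the absolute reading.
- **No within-arm test is specified.** The article describes mixed models over three time points and powers the secondary hypotheses on arm by time. The table above therefore illustrates what the first clause would invite, not a planned analysis. But that clause has no other possible test.
- **Regression to the mean is not equally direct everywhere.** Entry selects on youth diagnosis. Parents are not selected on a symptom threshold, so for parental mental health and relationships the argument rests more on natural change and other care.
- **Comparing effect sizes with other trials is ordinary benchmarking.** It is not given as a success criterion, and the effect sizes may themselves be between-arm. It is a secondary matter, though the stated purpose of determining relative efficacy goes further than description.

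**Conclusion.** The point holds for the first clause of secondary hypothesis (a) and for any reading of aim (a) as the efficacy of each program in itself. With two active arms and entry during a current disorder, neither can be identified, and no later analysis plan could supply the missing comparison.

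The chance of being misled depends on how much youth and parents would improve anyway, which the protocol does not state. At r = 0.20 it is about 5 to 70% without clustering for an assumed drift of 0.2 to 0.5 SD, and about 3 to 45% with the assumed group size of 8. At the low end the risk is small.

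A reader might infer that the trial's main conclusion is compromised. It is not: the primary hypothesis, the arm-by-time contrast and the greater-improvement clause rest on randomization and keep their error rates against natural recovery. This is a problem of stated aims and permitted conclusions, and it bites mainly if the arms turn out not to differ.

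**What to change.** 1. Restate aim (a) as the efficacy of BEST MOOD relative to PAST.
2. Restate secondary hypothesis (a) as a between-arm difference in change in parental and youth mental health and relationships. This is the contrast on which the article already powers the continuous secondary outcomes.
3. Report within-arm change, including reliable change, as descriptive, and state that it cannot be attributed to either program.
4. Describe the comparison with other trials as context only, and state that it does not support a claim that either program is effective in itself.

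The cost is rewording one aim, one hypothesis and the related analysis text. No visit, measure, sample size or primary analysis changes. The downside is that the trial gives up a claim that both programs work, which its design cannot support.

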### Eligibility criteria

#### Inclusion criteria

Families will be included in the study where there is an adolescent aged 12 to 18 years who is currently presenting with a depressive disorder. Specifically, the young person must, at the time of assessment, meet the criteria for either major depressive disorder, minor depressive disorder, or dysthymic disorder as assessed via current *DSM-IV* criteria.

#### Exclusion criteria

Exclusion criteria for the study are listed in Table 1. Specifically, in terms of diagnostic exclusions, youth who currently report any of the following will be excluded: mania, hypomania, a bipolar disorder, psychosis or psychotic disorders, an intellectual disability, a pervasive developmental disorders, drug dependence other than alcohol, nicotine or cannabis use, or any severe mental illness currently requiring inpatient treatment. Other than these listed diagnostic exclusions, other forms of co-morbidity will be accepted into the study, as long as a unipolar depressive disorder is the primary presenting issue (where this is in doubt clinical assessment with the senior clinical psychologist, CI [name] will determine eligibility). Other exclusions are if the parent/s or caregiver/s is/are unwilling or unable to attend and participate in a group, or if participating family members are unwilling or unable to complete the assessment process (as per Table 1).

**Table 1 T1:** Exclusion criteria

**Individual exclusions**	**Family exclusions**
^a^Mania, hypomania, or bipolar disorder	A current child protection investigation
An intellectual disability or a severe mental illness requiring inpatient treatment or otherwise impairing their ability to participate in a group program	The young person is unwilling to undertake the minimum requirements for entry to the study including completion of the consent form, telephone KID-SCID interview, and the baseline questionnaire
An inability to understand spoken English	The young person is currently pregnant
The parents indicate they are unable to participate fully in the program, including attendance at group sessions one evening per week for eight weeks and completing all questionnaires	Insufficient address for follow-up or unwillingness to be followed-up
^a^Psychosis or psychotic disorders, including drug induced psychosis	The young person is currently fully engaged and regularly attending a treatment service for their mental health problems which the family considers are adequately addressing their mental health needs
Pervasive developmental disorder, including autism but not including Asperger’s syndrome	
^a^Drug dependence, with the exception of alcohol, nicotine or cannabis	

Notes: ^a^ A history of these criteria does not exclude parents/caregivers from the study provided they have been asymptomatic/stable for several months.

### Recruitment

The flow of participants from recruitment through to end of study is shown in Figure 1, as adapted from CONSORT guidelines. A multifaceted recruitment strategy will be employed to recruit participants. Intake workers will be co-located with a local youth mental health service (the Eastern Health Child and Youth Mental Health Service (CYMHS) Access Team). Schools and agencies will be provided with information on the research study (marketed as the *Family Options* (FO) program), educated on the signs and symptoms of mood disorders, and will be asked to refer relevant families to the program. The research team will also directly market to the public via media releases, development of a website, utilizing the existing promotion media of partnership agencies and group Emails to local service providers. The research team will also host free education seminars for parents on parenting challenging teens, as a recruitment strategy. This strategy was found to be an effective recruitment tool in the pilot study [26].

**Figure 1 F1:**
[figure not shown]
CONSORT flow diagram of progress through the phases of the Family Options trial.

Enrollment into the trial will involve an intake worker conducting an initial telephone assessment with a parent or caregiver of the young person. This assessment will include: family demographic information, a genogram, a screen for inclusion and exclusion criteria, a the KID-SCID Mood Episodes Module B as reported by parents, and information on the young person and parent/s current mental health status and support services psychotropic medications, recent alcohol and other drug use and violence within the family, and risk assessments including suicide and self-harm risk. If the family is deemed eligible for participation in the trial, the intake worker will then confirm eligibility by administering selected modules of the KID-SCID to the young person. The selected modules are those for Major Depressive Disorder, Minor Depressive Disorder, and Dysthymic Disorder [28]. If the young person meets the inclusion criteria, the intake worker will then allocate to treatment condition using the randomized allocation sequence. Participants will be advised verbally and in writing that they will be free to withdraw at any stage upon request. Attempts will be made to assist families to find an alternative source of treatment, where possible, should they choose to withdraw at any stage.

### Randomization procedures and methods

Block randomization will be used following the procedure described in Altman and Bland [29]. It is desirable to have the number of participants allocated to each treatment condition similar at all times, in order to fill the treatment groups at approximately equal rates. The random number sequence will be generated by CI [name], in the following manner. Using blocks of four, there are only six possible ways of combining treatments A and B. Therefore for each sequence of four eligible families, both treatment conditions will be allocated twice. Six blocks will be generated. Using the website http://www.random.org, a random number series will be generated using numbers in the range of 1 to 6. A number will be allocated to each block. A second random number sequence will be generated for the allocation of blocks again. Blocks will then be arranged by going down each column until 200 conditions are allocated for Melbourne referrals, and a further 60 allocated for Geelong referrals. Finally a coin will be tossed where PAST = A and BEST-MOOD = B for heads, or PAST = B and BEST-MOOD = A for tails.

Sequentially numbered, opaque, sealed envelopes will be used to store the allocations, kept with the trial manager. Those allocating to treatment condition (intake workers) will be blinded to the randomization sequence and the overall study hypotheses.

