### Sample size and power

The trial aims to recruit a total of *n* = 160 participants. Based on pilot work and previously conducted clinical trials of family-based interventions compared to treatment-as-usual conditions, it has been estimated that it is possible to generate an effect size of *d* = 0.63 in reduction of mental health symptoms, which is equivalent to 14% increase in the odds of remission [45]. Out pilot data also indicates that treatment type by time interaction is able to produce up to 50% remission in depression diagnosis, over and above treatment type. With an alpha of 0.05 and power level of 0.90 for two-tailed tests, intraclass correlation coefficient (ICC) of 0.17 for within therapy group variation (estimated from our pilot data), and estimated 10% of variation in the main outcome accounted for by other variables in the model (treatment arm, time, parental socioeconomic status), the minimum sample size required equates to *n* = 57 per treatment arm. Based on pilot studies, an attrition rate of 20 to 25% is anticipated. Therefore, a minimum of 80 participants into each of the two treatment conditions will be recruited. Comparisons will be undertaken between those who drop out and those who are retained in order to assess for attrition bias.

With respect to our secondary hypotheses, anticipated final sample size of 114 individuals, will also allow us to detect small effect size (d = 0.23) for the treatment arm by time interaction for continuous outcomes, with 90% power and alpha level of 0.05, assuming ICC of 0.20 for within-person (between-assessment) and ICC of 0.07 for within therapy group variation (estimated from our pilot data).

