## Trial status

The trial is currently underway with participants currently being recruited and assessed. Date of first enrolment is 17 October, 2012. Estimated completion date is late 2014.

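### Fixed blocks of four, disclosed during recruitment and used by the person who confirms eligibility, make up to a third of allocations deducible, and the text does not place the youth baseline questionnaire before allocation

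*Protocol article*

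**What the plan says.** **Sequence.** Under Randomization procedures and methods the article states: "Using blocks of four, there are only six possible ways of combining treatments A and B". It continues: "Therefore for each sequence of four eligible families, both treatment conditions will be allocated twice". Lists are drawn up by region, "until 200 conditions are allocated for Melbourne referrals, and a further 60 allocated for Geelong referrals". The stated reason for blocking is to keep the arms near equal at all times so that the therapy groups fill at similar rates.

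**Concealment.** The same section puts the allocations in numbered, opaque, sealed envelopes held by the trial manager. Intake workers are said not to know the sequence or the study's hypotheses.

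**Who decides and who allocates.** In the enrollment paragraph under Recruitment, after the parent's telephone screen, "the intake worker will then confirm eligibility by administering selected modules of the KID-SCID to the young person". The paragraph then says: "If the young person meets the inclusion criteria, the intake worker will then allocate to treatment condition using the randomized allocation sequence". Under Exclusion criteria, doubt about whether depression is the main problem goes to a senior clinical psychologist. Positive psychosis screens also go to a senior clinical psychologist.

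**Entry requirements.** Table 1 excludes a family whose young person is unwilling to meet the minimum entry requirements, which include "completion of the consent form, telephone KID-SCID interview, and the baseline questionnaire".

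**Timing of disclosure.** Trial status: "The trial is currently underway with participants currently being recruited and assessed".

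**The concern.** There are two separate weaknesses around the moment of allocation.

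The first is predictability. One role judges entry and learns each result. With a constant block length, past results in a regional list carry information about the next one. Not knowing the sequence does not remove that information, because the block length and the previous assignments are enough. Eligibility leaves some room for judgement: minor depression qualifies, the KID-SCID is semi-structured, and depression must be the main presenting problem. A worker need not know the hypotheses to have a reason to lean one way. The Discussion reports difficulty in reaching the numbers needed to start groups on schedule, so which group the next family would join can matter in practice. If borderline entry decisions differed by expected arm, the arms could differ at baseline, and the remission comparison could be biased.

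The second is the order of steps. If a family can be allocated before the youth questionnaire is completed, a young person who then declines it fails an entry requirement with the arm already known. The article expects problems with questionnaire completion, and youth engagement is both an aim and a secondary hypothesis. Dropping such families would remove non-engagers after randomization.

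**Working it through.** **Inputs.** Block length four with two families per arm, and lists of 200 and 60 (Randomization procedures and methods). Planned total: "The trial aims to recruit a total of *n* = 160 participants" (Sample size and power).

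**1. The article's own figure.** Arrangements of two A and two B: 4!/(2! × 2!) = 6, as stated. The lists hold whole blocks: 200/4 = 50 and 60/4 = 15.

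**2. Allocations certain from earlier ones.** The six blocks are AABB, ABAB, ABBA, BAAB, BABA and BBAA, giving 6 × 4 = 24 positions.
- The fourth position is always determined: 6 positions.
- The third is determined when the first two match (AABB, BBAA): 2 positions.
- Total: 8/24 = 33.3%. Over 160 families, 160 × 8/24 ≈ 53.

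**3. Best guess.** Guess the arm that is behind, and toss a coin when the arms are level.
- Position 1: 1/2.
- Position 2: it differs from the first in 4 of 6 blocks, so 2/3.
- Position 3: certain in 2 of 6 blocks and a coin toss in 4 of 6, so 1/3 + (2/3 × 1/2) = 2/3.
- Position 4: 1.
- Sum: 1/2 + 2/3 + 2/3 + 1 = 17/6. Divided by 4, this is 17/24 = 70.8%, against 50% for an unpredictable sequence. Over 160 families, 160 × 17/24 ≈ 113.

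These figures require a worker, or workers who share information, to know the block length and follow every allocation within a regional list.

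**4. What other block lengths would do.** The same enumeration for fixed blocks of six gives 1.5 of 6 positions certain (25.0%) and 4.1 of 6 guessed correctly (68.3%). For an equal mix of fours and sixes, the correct-guess rate is (17/6 + 4.1)/10 = 6.93/10 = 69.3%. The guess rate falls by only about 1.5 percentage points, because guessing the arm behind does not need the block boundaries. Certainty does need them, so mixed, undisclosed lengths make it rare. The largest difference between arms within a list rises from 4/2 = 2 to 6/2 = 3 families.

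**5. Order of entry steps, side by side.** Table 1 names three requirements: consent, the telephone interview and the baseline questionnaire. The enrollment paragraph lists the parent screen, the youth interview and then allocation, with no questionnaire step. Assessments and outcome measures places the first assessment at enrollment without relating it to allocation. The flow figure is not available in the text reviewed. Nothing in the available text puts the questionnaire before allocation, and nothing puts it after.

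**The case against.** The safeguards are real. The envelopes are held by someone other than the intake worker, who is also blinded to the hypotheses, which weakens any motive to favor an arm. The two programs share the same length and format, a choice the Discussion links to fewer broken randomizations. Doubtful eligibility is not the intake worker's decision alone. The article refers to intake workers in the plural and keeps two lists, so no one person need see every allocation. It does not say that they are told the block length; publication makes it discoverable, not known. Small blocks also serve a stated purpose, filling groups evenly.

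All of this stands, and it makes the 33% and 71% ceilings rather than expected values. It does not remove the possibility of deduction: envelopes and blinding to the sequence leave past allocations visible to the person who made them, and that person makes the first eligibility judgement.

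On the questionnaire, a reader might infer that families will be excluded after allocation, contrary to intention to treat. The documents do not support that. Table 1 excludes on unwillingness, which can be established at screening. No text places the questionnaire after allocation, no rule removes allocated families, and intention-to-treat analysis is stated. What remains is an order that the two sections leave unreconciled.

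**Conclusion.** The point holds as a limited, cheaply removable weakness. Fixed blocks of four, disclosed while recruitment is open and used by the role that confirms eligibility, allow up to one third of allocations to be deduced with certainty and up to 71% to be guessed. Both figures assume knowledge of the block length and complete tracking of a regional list. A reader might go further and conclude that concealment has failed or that the comparison is already biased. The documents show neither: they describe an opportunity, not its use.

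Separately, the article should say where the baseline questionnaire falls relative to allocation. As written, exclusion after allocation is possible but not planned.

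**What to change.** 1. For the unused part of each regional list, prepare new envelopes with block lengths mixed at random, for example four and six, and do not disclose the lengths to anyone involved in recruitment. Change over at the end of a completed block.
2. Have the trial manager, who already holds the envelopes, release each one only after consent, the eligibility decision and the youth baseline questionnaire have been logged. This makes the eligibility decision final before the arm is known and settles the order between Table 1 and the enrollment paragraph.
3. State that every allocated family stays in the analysis under the existing intention-to-treat commitment, including any later found not to meet an entry requirement.

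The first step chiefly removes certainty and lowers the guess rate only slightly, so the second matters at least as much. The cost is a set of new envelopes and one line of procedure. The downsides are a possible difference between arms of three families rather than two within a region at any time, which bears slightly on filling groups, and a wait for the questionnaire before allocation.
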